### Interventions

**
Intervention arm: Yoga-based intervention for maternal Mental health and iMmunity (Yoga-M
_2_)
**

Participants randomized to the intervention arm will attend weekly supervised group yoga sessions and will also be requested to practice yoga regularly at home for a total duration of three-months. Group yoga session will be for 60 to 75 minutes. A typical session will begin with an introduction of the participants, a brief overview of the session by the yoga instructor and an opening prayer. This will be followed by
*sukshma-vyayam* (micro-circulation exercises) for 10 minutes,
*asanas* in standing, sitting, and supine position for 15 minutes,
*pranayama* for 15 minutes followed by
*shavasana* (deep relaxation) for 10 minutes. The session will end with a closing prayer. A detailed description of the yoga session is provided in
Table 1. After the session ends, the yoga instructor will spend time with each participant individually and suggest changes/modifications based on any problems they might have in practicing any of the yoga-based activities. Weekly group sessions will be conducted either in-person or online. In-person sessions will be preferred if allowed, depending on the COVID-19 pandemic-situation in the study area and restrictions in place. In-person sessions will be in a well aerated and ventilated hall. Use of sanitizers where appropriate and physical distancing will be maintained during yoga sessions. Participants can also attend group yoga sessions online via
Zoom. The plan is to have five in-person group yoga sessions over five days in the beginning to teach the entire yoga sequence to the participants. This will be followed by weekly group yoga sessions. We anticipate that each participant will attend 10 group yoga sessions over 12 weeks.

**Table 1. T1:** Yoga-based intervention for maternal Mental health and iMmunity (Yoga-M
_2_).

	Type of Activity	Duration (Second Trimester)	Duration (Third Trimester)
**1.**	**Opening Prayer** ‘Om, Sahana Vavatu Sahana Bhunattu Saha Viryam Karawavahai Tejasvinavaditamastu Ma vidvishavahai Om, Sāntih Sāntih Sāntih’	**3 minutes**	**3 minutes**
2.	** *Sukshma-Vyayam* ** **(Micro-circulation exercises)**	**10 minutes**	**5 minutes**
	*Griva Sanchalan* Neck movements	Yes	Yes
	*Skandha Paribhraman* Shoulder rotation	Yes	Yes
	*Hasta Ayama Svasanam* (Hands in and out breathing)	Yes	Yes
	*Hasta Vistara Svasanam* (Hands stretch breathing)	Yes	Yes

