Assessment of acceptability of the intervention will also be done using a structured satisfaction survey and a qualitative study. In-Depth Interviews (IDIs) with all yoga instructors and enrolled participants will be completed. Semi-structured interviews will cover themes related to the delivery, content, comfort, and complexity of the intervention. We plan to enroll around 15 participants (10 from the intervention arm and 5 from the control arm), however, the sample size for the qualitative study will be determined by data saturation.

The description of measures which will be used to assess the preliminary efficacy of the intervention is given in
Table 3.

**Table 3. T3:** Measures to assess the preliminary efficacy.

Outcome	Measure	Time-point
Stress	Perceived Stress Scale (PSS)	Baseline and three-months post-randomization
Quality of Life	EuroQoL 5 Dimensions Score (EQ-5D-5L)	Baseline and three-months post-randomization
Immune Function	Wisconsin Upper Respiratory Symptom Severity Scale	Baseline and three-months post-randomization
Immune Function	Serum C-Reactive Protein	Baseline and three-months post-randomization
Injuries due to yoga	Self-report log	Every week for three-months post-randomization
Serious Adverse Events (SAE)	SAE report form	Baseline and three-months post-randomization

**
Perceived Stress Scale (PSS)
**

Perceived stress will be measured using 10-item version of the original scale
^
22
^. The items in this instrument assess how unpredictable, uncontrollable, and overloaded participants appraise the situations in their lives in last one month. PSS has been widely used in research studies across the globe and it has acceptable psychometric properties
^
23
^. In this study, we will use the Marathi version of the PSS which was translated from the English version using the World Health Organization (WHO) guidelines for the process of translation and adaption of instruments
^
24
^.

**
EuroQoL 5 Dimensions Score (EQ-5D-5L)
**

European Quality of Life Five Dimension (EQ-5D-5L) descriptive system will be used to measure Health related Quality of Life (HRQoL). A single utility score will be calculated using the value set/preference weights for Thailand as the Eq-5D value set for India is under development
^
25
^. Participants will also provide an overall evaluation of their health using a visual analogue scale (VAS). We will use the Marathi version of EQ-5D-5L with permission from the EuroQoL Group
^
26

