^. The EQ-5D has been validated in different parts of the world
^
27
^. 

**
Wisconsin Upper Respiratory Symptom Severity Scale (WURSS)
**

The incidence and severity of upper respiratory tract infections in the participants will be assessed using the
Wisconsin Upper Respiratory Symptom Survey (WURSS-21). This is a 21-item scale; 10 items assess symptoms, nine items assess functional impairments, and there is one item each to assess the overall severity and change. Responsiveness, reliability, convergence, and importance to patients of this scale have been validated
^
28
^. Participants will complete WURSS-21 at the end of each day in the study. We will use the Marathi version of WURSS with permission from the developers.

**
Serum C-Reactive Protein (CRP)
**

Serum CRP levels will be determined using fixed-point immune-rate method (VITROS 250/350/5, 1 FS/4600/XT 3400 Chemistry Systems and the VITROS 5600/XT 7600 Integrated Systems). The limit of detection for VITROS Chemistry Products CRP slides is 2.72 mg/L.

**
Self-report log
**

Participants in both arms will maintain a log to document any injuries/non-serious adverse events during the duration of the trial.

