### Oversight and monitoring

**
Composition of the coordinating centre and trial steering committee
**

The Trial Management Group (TMG) will coordinate the day-to-day implementation of the trial. The Trial Steering Committee (TSC) will provide the oversight for the trial. TMG will comprise of the principal investigator, the RAs, the IC, ST, a clinician, and a patient representative. It will meet every two weeks. The TSC will meet every four weeks. It will be headed by an independent chairperson and there will be four other members. There will be representatives of the TMG on the TSC.

**
Composition of the data monitoring committee, its role and reporting structure
**

Due to the nature of the trial and low risk for participants, the TSC will also take on the role of the data monitoring committee. During the TSC meetings, data related to progress of the trial and safety of participants will be reviewed and discussed.

**
Adverse event reporting and harms
**

Previous evidence suggests that yoga during pregnancy is safe
^
30
^ and no adverse events have been reported in an earlier trial by Satyapriya
*et al.*
^
19
^. Records of all Serious Adverse Events (SAEs) will be maintained in a log by the CRC.

1) Death due to any cause2) Hospitalization due to any cause3) Suicide attempt4) Spontaneous abortion or stillbirth

SAEs in both arms will be documented by the RAs at three-month follow-up assessment. The IC and yoga instructors will also be trained to identify SAEs and notify them to the CRC. Within two weeks of becoming aware of any SAE (related or unexpected), the Institutional Ethics Committee will be informed about the same by PI. A standard operating procedure will include all the details pertaining to the detection, appropriate response and reporting of SAEs. If any SAE requires an immediate response, an independent medical specialist will do so within two working days. The criteria for unblinding of adverse events will be set
*a priori*. A summary of all adverse events will be sent to the Institutional Ethics Committee, the funder, and the TSC regularly as part of the progress report.

All necessary and appropriate medical assistance will be provided to participants in the PIMS for injuries related to participation in the trial (intervention arm). There will be no financial burden on the participants for trial related injuries and adverse events.

**
Frequency and plans for auditing trial conduct
**

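### Between randomization and three months the stated SAE routes are unequal: Yoga-M2 women have about ten planned contacts with SAE-trained staff, EUC women one, so interim safety data are likely to arrive earlier for Yoga-M2

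*Protocol article*

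**What the plan says.** The relevant statements are spread over several sections of the protocol article.

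- **Common route.** Under Adverse event reporting and harms: "SAEs in both arms will be documented by the RAs at three-month follow-up assessment". In Table 3 (Outcomes) the measure is the "SAE report form", at baseline and three months. The RAs are blinded (Who will be blinded?). The section on participant retention gives a reminder call, a seven-day window, and a home visit for women who cannot come to the clinic.
- **Added route.** "The IC and yoga instructors will also be trained to identify SAEs and notify them to the CRC". The sentence names no arm.
- **Contact with that route.** For Yoga-M2: "We anticipate that each participant will attend 10 group yoga sessions over 12 weeks". The section on adherence adds regular contact by the IC and instructor, and an IC home visit once two weekly sessions in a row are missed. For EUC, one health-education session with the IC is planned.
- **Log.** "Participants in both arms will maintain a log to document any injuries/non-serious adverse events during the duration of the trial". Table 3 gives its timing as "Every week for three-months post-randomization".
- **Oversight.** The TSC meets every four weeks and also serves as the data monitoring committee: "During the TSC meetings, data related to progress of the trial and safety of participants will be reviewed and discussed".
- **Deferred detail.** "A standard operating procedure will include all the details pertaining to the detection, appropriate response and reporting of SAEs".
- **Pregnancy loss.** It is one of the four listed SAEs and ends participation in either arm. The article does not say whether SAE follow-up then continues.

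**The concern.** Staff trained to recognise and notify SAEs see one arm repeatedly and the other hardly at all. The four listed SAEs are death, hospitalization, suicide attempt, and spontaneous abortion or stillbirth. In Yoga-M2 such an event tends to show itself, because the woman stops attending and absence prompts a home visit. Nothing comparable is stated for EUC. Minor events are to be logged weekly in both arms, yet the serious ones are asked about once after randomization.

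Two things are at stake. First, the TSC's interim picture may contain Yoga-M2 events and lack EUC events from the same weeks. With 25 women per arm, one or two unseen events could change it. Even if the TSC sees only a total, that total is incomplete. Second, there is the welfare of EUC women. A suicide attempt or hospitalization may become known late, and the two-week period for informing the ethics committee starts only when the study becomes aware.

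**Working it through.** The article gives no SAE rate or detection figure, so there is no plan figure to reproduce. The check compares the stated schedules and then bounds the delay.

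**1. Stated routes after randomization**

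| Route | Yoga-M2 | EUC |
|---|---|---|
| Blinded RA enquiry, clinic or home | once, at three months | once, at three months |
| Planned sessions with IC or instructors | about 10 | 1 |
| Regular contact by IC or instructor | yes, interval not given | none stated |
| Home visit triggered by absence | after two missed weekly sessions | none stated |
| Weekly self-report log | no SAEs | no SAEs |

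The IC also meets every woman when the envelope is opened, but no follow-up time has passed by then.

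**2. Delay in EUC if an event is learned of only at the RA assessment**

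Assumptions: three months is 91 days; the seven-day window extends this to day 98; events are even over time; the single EUC session falls near day 0.

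- Mean delay = length / 2: 91/2 = 45.5 days; 98/2 = 49 days.
- Longest delay: 91 to 98 days.
- Four-weekly TSC meetings passed on average: 45.5/28 = 1.63; 49/28 = 1.75.
- Meetings within the whole period: 91/28 = 3.25 to 98/28 = 3.5, so at most 3 or 4.

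These are upper bounds, because the IC or someone else may hear sooner.

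**3. The timed trigger in Yoga-M2**

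A woman with one of these events may well not attend the next session, so the gap between sessions is not a fair measure of delay. The only absence rule with a stated time is two missed weekly sessions. For an event between weekly sessions, the first missed session follows 0 to 7 days later (mean 3.5) and the second 7 days after that. The rule is therefore met after 7 to 14 days, mean 3.5 + 7 = 10.5 days. The article sets no deadline for the home visit, so awareness by this path is no earlier than that. Regular contact may bring news sooner. EUC has no such rule.

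**4. Final comparison**

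The RA form is completed in both arms at the same time by blinded staff. If it captures every event, the arms are compared on equal terms and only the timing of awareness differs. Completeness could differ if the CRC log, which pools all sources, were compared by arm. The comparison is also at risk if women are not assessed after pregnancy loss, death or loss to follow-up. The three-month interview is timed with an antenatal check-up, which a woman who has lost her pregnancy no longer attends.

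**5. With the same four-weekly enquiry in both arms**

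Mean delay = 28/2 = 14 days, maximum 28 days, in both arms.

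**The case against.** The strongest reply is that detection is expressly left to a standard operating procedure, which is not shown and may provide equal interim enquiry. That stands as a limit on the finding. But the article does more than defer: it names the persons and the time points, and what it names is unequal. It is also true that the added route is not restricted to Yoga-M2. The IC and instructors are to see that women in both arms keep to their allocation, so the IC may hear of some EUC events. No EUC contact schedule is given, however.

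A reader might draw stronger conclusions that the documents do not support:

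- **That the final SAE comparison is biased.** Table 3 ties the SAE measure to the form at fixed visits, completed by blinded RAs. No by-arm comparison of the pooled CRC log is planned.
- **That a woman who misses the clinic visit is never asked.** The article provides a seven-day window and a home visit. The gap is confined to women who are not assessed at all.
- **That 10% loss is expected.** The 10% in the missing-data section is a trigger for multiple imputation, not a forecast.
- **That Yoga-M2 events would be known at the very next session.** These are events that tend to keep a woman away.
- **That follow-up stops after pregnancy loss.** The article says that participation is discontinued and is silent on SAE follow-up.

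Finally, extra contact with EUC women adds attention to a deliberately light comparator and gives more chances to disclose allocation, in a pilot described as low risk. That is a reason to use the existing log rather than calls to every woman.

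**Conclusion.** The point holds as a matter of interim ascertainment and timing. On the stated schedule, SAEs in Yoga-M2 are likely to reach the CRC and the TSC earlier than SAEs in EUC. An EUC suicide attempt, hospitalization or pregnancy loss may surface only at about three months. The contact contrast is about 10 planned sessions against 1. In the worst case for EUC the mean delay is 45.5 to 49 days, or 1.6 to 1.75 TSC meetings. This rests on events being even over time, no earlier report by any other path, and no further route in the standard operating procedure. The direction follows from the schedule; the size is illustrative.

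The three-month comparison on the RA form is sound in method. It is at risk only if the pooled log is compared by arm, or if women go unassessed after pregnancy loss, death or loss to follow-up. The change is worth making because it is cheap and because this pilot is meant to settle the evaluation strategy for a larger trial.

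**What to change.** 1. Add the four listed SAEs to the self-report log that both arms already keep. State that logs are reviewed on the same schedule in both arms, for example before each four-weekly TSC meeting, and amend the SAE row of Table 3 to match.
2. Use a short scripted call only where a written log cannot be kept, as for women who cannot read or write Marathi. A log that is not returned should prompt a call to the household, which also covers deaths. The caller should have no access to the allocation record, so not the IC, the instructors or the CRC, and should repeat the reminder not to reveal the group.
3. State that SAE follow-up to three months continues after discontinuation for pregnancy loss.
4. Record the source of each SAE and base the arm comparison on the common route. Keep IC and instructor reports for immediate response.

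Cost: four lines in an existing log, one table row, and a few sentences under the discontinuation criteria and adverse event reporting. No new visit or committee is needed. Calls on a four-weekly schedule come to about three for each woman who needs them. The downside is a small extra workload and slightly more contact with EUC women.

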**Qualitative ** **Study**	• 10 in-depth interviews with pregnant women to explore facilitators and barriers to yoga practice • Three focus group discussions with community health workers to assess the feasibility of conducting group sessions in the community settings.	• Community hall or *anganwadi* center to deliver group yoga sessions instead of a hospital setup as pregnant women preferred a location close to their homes. • Modifications in a few *asanas* as some pregnant women will be able to attend the sessions wearing *saree* (a long piece of cloth draped around the body and over one shoulder, worn by women in India). • Recruitment of participants in the antenatal clinical of PIMS, as the community health workers suggested that treating obstetrician should approve the practice of yoga by pregnant women.
**Intervention ** **Adaptation ** **Workshop**	• Two intervention adaptation workshops; one with four pregnant women and other with three pregnant women were conducted to get their feedback on the modified yoga sequence.	• No changes were made in the modified sequence as all the participants provided positive feedback on the modified yoga sequence.

**
Comparison arm: Enhanced Usual Care (EUC)
**

Participants randomized to the EUC arm will receive a single session of health education delivered by the Intervention Coordinator (IC). During this session, aspects related to sleep hygiene and diet during pregnancy will be discussed and they will be encouraged to undertake regular physical activity (150 min/week). They will be provided educational leaflets containing information about physical activity, sleep, and diet during pregnancy. The IC will work with the participants to identify ways to reduce stress during pregnancy and improve social support. As per the current standard of care in the antenatal clinic of Department of Obstetrics, pregnant women are neither screened for stress nor is there any discussion about improving mental health during pregnancy. Participants with moderate stress (Perceived Stress Scale score > 13) will be referred to a psychiatrist in PIMS.

**
Criteria for discontinuing or modifying allocated interventions
**

If there is spontaneous abortion or stillbirth, participation in both the arms will be discontinued. Other than this, there is no specific criteria to discontinue Yoga-M

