_2_ intervention. A few modifications in the sequence for individual participants may be done by the yoga instructor based on feedback from them. Obstetrician may advise participants to discontinue yoga due to health issues or they may decide to stop practicing yoga themselves for any reason.

**
Strategies to improve adherence to interventions
**

The IC and the yoga instructor will regularly contact participants in Yoga-M
_2_ arm to coordinate attendance in weekly group yoga sessions. If a participant misses two consecutive weekly group yoga sessions, the IC will visit the participant at home to address any barriers related to joining the session. Adherence to home practice will be assessed using home practice logs. 

**
Relevant concomitant care permitted or prohibited during the trial
**

Throughout the duration of the trial, participants will receive usual care and no specific component of antenatal care or other health services will be prohibited.

**
Provisions for post-trial care
**

Participants in both arms will receive information about yoga classes they can join after the end of the trial. Participants in the control arm will also receive the yoga intervention booklet and the audio-visual material. Participation in yoga classes post-trial will be entirely voluntary and on a self-pay basis. No compensation will be provided to participants who suffer non-negligent harm from trial participation.

**
Outcomes
**

Outcome assessment will include measures related to:

a) feasibility and acceptability of yoga-based intervention (Yoga-M
_2_) deliveryb) preliminary efficacy of Yoga-M
_2_

Feasibility and acceptability will be assessed using the following process data:

1. Number and proportion of eligible participants who are recruited per week in each arm.2. Number and proportion of recruited participants in Yoga-M
_2_ arm who attend the in-person yoga sessions.3. Number and proportion of recruited participants in Yoga-M
_2_ arm who attend at least 50% of the follow-up yoga sessions.4. Number and proportion of recruited participants who complete follow-up assessment three-months post-randomization in each arm.

Process data will be collected from the study enrollment logs and intervention delivery logs. Study enrollment logs will be maintained by RAs and intervention delivery logs will be maintained by the IC. Every week this data will be manually entered and stored as CSV files on an access-restricted computer.

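### The safety section allows two working days for the response to a serious adverse event that it says needs an immediate one

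*Protocol article*

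**What the plan says.** All the main text is in the Protocol article, Oversight and monitoring, under Adverse event reporting and harms.

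- The SAE list is: "1) Death due to any cause2) Hospitalization due to any cause3) Suicide attempt4) Spontaneous abortion or stillbirth".
- During the trial, events may reach the team through non-clinical staff: "The IC and yoga instructors will also be trained to identify SAEs and notify them to the CRC". Research assistants also record SAEs in both arms at the three-month visit.
- Reporting has its own limit: "Within two weeks of becoming aware of any SAE (related or unexpected), the Institutional Ethics Committee will be informed about the same by PI".
- Detail is deferred: "A standard operating procedure will include all the details pertaining to the detection, appropriate response and reporting of SAEs". That procedure is not shown.
- The response rule is: "If any SAE requires an immediate response, an independent medical specialist will do so within two working days".

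Two other statements bear on care. The same section promises medical assistance at the study hospital for trial-related injuries, marked as applying to the intervention arm, and adds: "There will be no financial burden on the participants for trial related injuries and adverse events". The section on concomitant care states that "participants will receive usual care and no specific component of antenatal care or other health services will be prohibited".

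**The concern.** The response rule is at odds with itself. Its condition picks out events that cannot wait, and its main clause then sets a limit measured in working days. The words *will do so* have only one thing to refer to, which is the response named in the condition.

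What is at stake is the instruction that trial staff receive. A suicide attempt or a pregnancy loss could first come to light through the intervention coordinator or a yoga instructor. Someone in that position who looks to the protocol for the required speed of response finds a single limit, two working days, attached to a single actor, an independent specialist. A team that met that limit would be compliant, even though the event had been classed as needing an immediate response.

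**Working it through.** There is no formula behind the two-day limit and no statistical figure to reproduce. The check is a comparison of texts, followed by a short calendar calculation.

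**1. What the limit governs.** It is not a reporting deadline, because notification of the ethics committee is timed separately at two weeks and assigned to the principal investigator. The sentence names no other task, such as review, causality assessment or advice to the steering committee. On its wording, the limit applies to the response.

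**2. Whether other text corrects it.**

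| Provision | Does it set a faster response to an urgent SAE? |
|---|---|
| Medical assistance at the study hospital | No. It covers trial-related injuries, is marked for the intervention arm, and has no time limit. |
| No cost to participants for trial-related injuries and adverse events | No. It concerns payment, not timing. |
| Usual care unrestricted | No. It leaves care open to the woman but gives staff no instruction on learning of an event. |
| Psychiatric referral for a Perceived Stress Scale score above 13 | No. A score triggers it, not an SAE. It is untimed and described under the comparison arm. |
| Operating procedure for SAEs | Unknown. It may add an urgent step, but it cannot be assumed to override a limit that the protocol states. |

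The two-working-day limit is the only timed clinical response to an SAE in the article.

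**3. Which events are affected.** Of the four listed types, a death leaves no urgent referral to make, and a hospitalised woman is already in care. The rule matters chiefly for a suicide attempt and for spontaneous abortion or stillbirth, when first reported to trial staff.

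**4. The limit in calendar days.** The protocol does not say which days are working days or when the clock starts. Assume that it starts on the day the team learns of the event and that this day is not counted.

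- Monday-to-Friday week, notified Friday: Monday is working day 1 and Tuesday is working day 2, so Friday to Tuesday = 4 calendar days. Notified Thursday: Friday is 1 and Monday is 2, again 4 days. Notified Monday: Wednesday, 2 days. The range is 2 to 4.
- Monday-to-Saturday week, notified Friday: Saturday is 1 and Monday is 2, so 3 days. Notified Monday: 2 days. The range is 2 to 3.
- If the day of notification counts as working day 1, a Friday report in a Monday-to-Friday week is due on Monday, after 3 days.

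A public holiday would lengthen any of these. They are the longest times the rule permits, not delays to be expected.

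**The case against.** The strongest reply is that the sentence describes oversight, not bedside care. It sits among sentences on ethics notification, the operating procedure and the criteria for unblinding. An independent medical specialist fits a reviewing role better than that of first responder. On that reading two working days is reasonable and the fault is loose wording. This is plausible, and it may well be what was intended. It does not rescue the text, because the sentence mentions neither review nor any earlier emergency care.

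A second reply is that response detail is left to the operating procedure, and that a journal article need not reproduce it. That is right as far as missing detail goes, and the absence of such detail is no part of this point. The point is a limit that the article itself states. A procedure written to match would inherit that limit, and a stricter one would conflict with it.

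A third reply is that the practical reach is small. *Within* sets a maximum, many SAEs may be recorded only in retrospect at three months, and usual care is open to every participant. All of this stands, and it limits the weight of the point.

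Two stronger readings are tempting. A reader might infer that women would be left without care for up to two working days. The document does not support that, since no text tells staff to delay or withhold care and usual care is unrestricted in both arms. A reader might also infer that the protocol has deliberately folded urgent referral and specialist review into one step. The sentence uses neither term, so the most that can be said is that it does not state which task the limit covers.

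**Conclusion.** The point holds as a defect in a stated rule. A response on the second working day complies for an event classed as needing an immediate one, and no other text in the article corrects this. The permitted time is up to about 4 calendar days over a weekend with a Monday-to-Friday week, or 3 with a Monday-to-Saturday week. Both figures rest on the assumption that the clock starts on, but does not count, the day of notification.

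The conclusion that the rule is wrong as written does not depend on those calendar assumptions; the clash is within the sentence. The practical consequence is confined mainly to suicide attempts and pregnancy losses that reach trial staff first. There is no evidence that care would be withheld, and neither the sample size nor any analysis is touched. It should be corrected because it concerns participant safety and the correction is simple.

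**What to change.** Replace the sentence with:

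> Any team member who becomes aware of an SAE needing an immediate response, in either arm, will immediately refer the participant to emergency care (PIMS or the nearest facility) unless she is already under care; an independent medical specialist will review the event within two working days.

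The operating procedure for SAEs should be aligned with this wording. The two-day limit is kept, for the task it suits. If the authors meant something else by it, they should say what it covers, but the immediate step should still be stated.

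The cost is one sentence in the protocol and a matching line in the procedure. The protocol's amendment section already provides a route for changes that affect participant safety, through the steering committee, the sponsor and the ethics committee.
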